## Abstract

**Background:**

The prevalence of smoking remains high in many low- and middle-income countries (LMICs), including the Southeast Asian nation of Cambodia. Smoking is especially hazardous for people with HIV. In Cambodia, approximately 43%-65% of men with HIV and 3%-5% of women with HIV smoke cigarettes. Thus, there is a critical need for cost-effective smoking cessation interventions for Cambodian people with HIV. This paper describes the design, methods, and data analysis plans for a randomized controlled trial assessing the efficacy of a theory-based mobile health smoking cessation intervention in Cambodian people with HIV.

**Objective:**

This 2-group randomized controlled trial compares the efficacy of a mobile health–based automated messaging (AM) intervention versus standard care (SC) in facilitating smoking cessation among Cambodian people with HIV.

**Methods:**

Cambodian people with HIV who currently smoke and are receiving antiretroviral treatment (target, N=800) will be randomized to (1) SC or (2) the AM intervention. SC participants will receive brief advice to quit smoking, written self-help materials, nicotine patches, and will complete weekly app-delivered dietary assessments for 26 weeks. AM participants will receive all SC components (but will complete smoking-related weekly assessments instead of dietary assessments), in addition to a fully automated tailored messaging program driven by the weekly assessments to facilitate smoking cessation. In the Phase-Based Model of smoking cessation, the cessation process is partitioned into 4 phases: motivation, preparation (precessation), cessation (quit date to 2 weeks post quit), and maintenance (up to 6 months post quit). Our AM program targets processes within these phases, including increasing motivation to quit, enhancing self-efficacy, obtaining social support, skills to cope with nicotine withdrawal symptoms and stress, and skills to maintain abstinence. All participants will complete baseline and 3-, 6-, and 12-month in-person follow-up assessments. The primary outcome is biochemically confirmed abstinence at 12 months, with 3- and 6-month abstinence as secondary outcomes. Potential mediators and moderators underlying treatment effects will be explored, and cost-effectiveness will be assessed.

**Results:**

This study was approved by all relevant domestic and international institutional and ethical review boards. Participant recruitment commenced in January 2023. Data collection is expected to conclude by the end of 2025.

**Conclusions:**

By demonstrating the greater efficacy and cost-effectiveness of AM relative to SC, this study has the potential to transform HIV care in Cambodia and prevent tobacco-related diseases. Furthermore, it may be adapted for use in other Cambodian populations and in other low- and middle-income countries. Ultimately, the AM approach to smoking cessation could greatly improve public health in the developing world and beyond.

**Trial Registration:**

ClinicalTrials.gov NCT05746442; https://clinicaltrials.gov/ct2/show/NCT05746442

**International Registered Report Identifier (IRRID):**

PRR1-10.2196/48923

## Introduction

Tobacco use remains the leading cause of preventable morbidity and mortality worldwide [1]. Although the prevalence of tobacco use has declined in high-income nations in recent decades, the prevalence of smoking remains strikingly high in many low- and middle-income countries (LMICs) [2]. In Cambodia, for example, national surveys have indicated that 33%-43% of adult men and 3% of adult women smoke cigarettes [3,4]. Thus, the development and evaluation of sustainable tobacco cessation interventions suitable for widespread implementation in Cambodia are pressing public health needs.

Certain special populations, such as people with HIV, are confronted with disproportionately high tobacco-related health risks. Data from high-income nations indicate that tobacco use represents a leading cause of mortality among people with HIV [5-10]. Nonetheless, there are few efficacious tobacco cessation interventions for people with HIV. The problem of tobacco use among people with HIV appears to be even more critical in Cambodia: available estimates indicate that 43%-65% of men with HIV and 3%-5% of women with HIV smoke cigarettes [11,12]. Although Cambodia has widespread coverage for antiretroviral treatment (ART), no known efforts have been made to provide tobacco treatment to ART recipients who smoke. Thus, complementing ART with efficacious tobacco cessation treatment offers tremendous potential to improve HIV care and prolong life for people with HIV.

This paper describes the design, methods, and analysis plans for an ongoing intervention trial with pharmacological and behavioral treatment components, including a fully automated, smartphone-delivered intervention. Mobile health (mHealth) interventions are proliferating in the United States, but efforts to use similar approaches in Cambodia are extremely limited. The World Health Organization (WHO) acknowledges that the use of mobile and wireless technologies for health promotion is cost-effective, scalable, and sustainable for the least developed countries [13]. In addition, text messaging interventions for smoking cessation have been shown to be effective [14,15], cost-effective [16], and very affordable for tobacco control globally [17-19].

We previously developed the mHealth-based intervention approach discussed in this paper and completed a pilot study with 50 Cambodian people with HIV who smoked and received care at an ART clinic. The results indicated that the biochemically confirmed, 7-day point prevalence abstinence rates at the 2-month follow-up were 40% in the group receiving the mHealth intervention versus 8% in the standard care (SC) control group (relative risk 5.0, 95% CI 1.2-20.5) [20]. This study will evaluate the long-term efficacy of this intervention with a fully powered sample size.

In this study, we are conducting a 2-group randomized controlled trial (RCT) to fully evaluate our mHealth-based automated messaging (AM) intervention versus an SC approach among Cambodian people with HIV who smoke. Specifically, we will assess the long-term (12 months) efficacy of AM, and we will conduct an economic evaluation to compare its cost-effectiveness to that of SC. We will also explore potential mediators and moderators underlying the associations between AM treatment and smoking abstinence (Multimedia Appendix 1).

## Methods

### Ethics Approval

Funding for this study was provided by the National Cancer Institute in 2021 (U01 CA261598-01). It was approved by Moffitt Cancer Center’s institutional review board (IRB; Advarra), which was selected to serve as the single IRB of record for the research described in this protocol by all participating domestic institutions (#00000971), while the IRB of the Ministry of Health of Cambodia—the Cambodian National Ethics Committee for Health Research—approved the research conducted at sites in Cambodia (NECHR #092).

### Study Design

We are using a 2-group RCT to compare the efficacy of 2 smoking cessation interventions: our already-developed smartphone-delivered AM intervention versus SC. Participants are people with HIV recruited through ART clinics in Phnom Penh. Following consent, participants will be randomly assigned to 1 of the 2 study groups: SC (n=400) or AM (n=400). Participants will be asked to complete in-clinic assessments at baseline, and at 3-, 6-, and 12 months following study enrollment (Figure 1). All participants also will complete brief weekly assessments via smartphone. All staff-participant interactions will be conducted to mitigate the potential spread of SARS-CoV-2 and other infections. Should COVID-19–related risks increase in Phnom Penh, we will adapt our procedures by conducting all assessments and follow-ups remotely.

**Figure 1 figure1:**
[figure not shown]
Trial schema. CO: carbon monoxide.

### Conceptual Framework for AM

Our AM intervention is based on the Phase-Based Model (PBM), a theoretical framework that is specific to smoking cessation [21]. The PBM partitions the cessation process into 4 phases: motivation, preparation (precessation), cessation (quit date to 2 weeks post quit), and maintenance (up to 6 months post quit); our project focuses on the 3 latter phases. The PBM helps to identify challenges and opportunities that smokers face at each phase, explains underlying phase-specific mechanisms, and facilitates the selection of intervention components and measures. Several putative mechanisms are relevant across phases and have been empirically shown to be reliably associated with long-term abstinence. These include withdrawal or craving, motivation to quit, positive or negative affect, coping with stress and urges, self-efficacy, and perceived support [21-25]. As such, the AM intervention specifically targets these mechanisms.

### Participants and Eligibility

There are currently 12 ART clinics or hospitals in Phnom Penh that serve approximately 18,800 registered ART patients [26]. We will begin recruitment at sites that serve larger volumes of patients but may add additional clinic sites as needed to reach our accrual goals. Services provided include ART, ART adherence and risk-reduction counseling, nutrition education, and treatments for comorbidities other than tobacco use. Of the ART patients seen at these clinics or hospitals, >90% are of Khmer ethnicity, 49% of them are men, and 93% of them are aged ≥18 years [12,26,27]. The mean levels of education are seventh grade for men and fourth grade for women [28]. The mean duration of ART is 5.7 years. Registered patients at the clinics have periodic prescheduled appointments (about once per month for ART), further facilitating screening and tracking. Study inclusion criteria are: (1) aged ≥18 years; (2) HIV positive; (3) self-report of current combustible cigarette smoking (smoked ≥100 cigarettes in a lifetime and currently smoke ≥1 cigarette per day); (4) willing to set a quit date within 2 weeks of study enrollment; (5) able to provide written informed consent; and (6) able to read Khmer (score ≥4 points on the Rapid Estimate of Adult Literacy in Medicine—Short Form [29]). Exclusion criteria are (1) history of a medical condition that precludes the use of nicotine replacement therapy (NRT), (2) physician or clinician deemed ineligible to participate based on medical or psychiatric condition, or (3) enrolled in another cessation program or use of other cessation medications.

### Baseline Assessment and Randomization

All eligible individuals will be invited to participate. Individuals interested in participating in the study will complete the informed consent process. Enrolled participants will be instructed to complete a tablet-delivered baseline computer-assisted self-interview (CASI), which is managed and delivered by an electronic data capture platform [30-32]. The use of an electronic data capture system that contains programmed logic checks and skip patterns enhances both accurate data collection across sites and timely and secure data transmission. Research staff will help participants complete the assessment if needed. The baseline assessment will take approximately 40 minutes to complete. Enrollees will be randomized to SC or AM via stratified randomization, with sex assigned at birth serving as the stratification variable. All participants will subsequently complete a brief training session on smartphone use and the smartphone app. Smartphones will be loaned to participants who need them. These procedures were followed in our pilot and were found to be feasible in the ART setting.

### Intervention Conditions

#### Standard Care

Participants randomized to SC receive brief advice to quit smoking delivered by trained research staff and self-help materials, including 2 fliers and a 32-page booklet. These self-help materials are from Khmer Quit Now, a national smoking cessation campaign in Cambodia, and are based on the WHO’s “A guide for tobacco users to quit [33].” Participants also receive an 8-week supply of NRT in the form of nicotine patches, which is consistent with US Food and Drug Administration recommendations and has been found to double cessation rates in meta-analyses [34,35]. SC participants complete brief weekly smartphone assessments (4 items) about their diet for a 26-week period. The dietary assessments are included to approximately equate the 2 conditions on the number and frequency of assessments.

#### Automated Messaging

Participants in the AM group receive the SC components (with the exception of the dietary assessments) plus proactive personalized messages for smoking cessation. The AM content was adapted from the team’s previous efforts and designed to tap the theoretical mechanisms described in the PBM (see Conceptual Framework for AM) [20,36,37]. That is, treatment content is designed to increase motivation, self-efficacy, use of coping skills, and social support and to reduce nicotine withdrawal symptoms and stress. The AM treatment begins immediately after enrollment and continues for a 26-week period. The Insight platform is used to manage and deliver the AM intervention and all weekly assessments [38]. The AM intervention approach allows for several levels of personalization for each participant, as it leverages the adaptive capabilities of the Insight platform. First, at baseline, participants are asked several questions about past quit attempts, preferred coping skills, and the presence or fear of specific health conditions. Messages tailored to these responses are delivered automatically throughout the treatment period. Second, there are different messages for different cessation phases to ensure that the AM intervention targets critical mechanisms of each phase. Phase identification is based on modified PBM definitions; specifically, preparation (enrollment to quit date), cessation (quit date to week 4 post quit date), and maintenance (weeks 4-26 post quit date) [39]. Third, participants are asked to complete brief (4-8 items) smartphone-delivered assessments during each week of the AM treatment course. Some questions vary depending on the phase (eg, current level of intrinsic motivation for preparation or maintenance phases) and other questions are asked in all phases (eg, smoking status in the past week and self-efficacy level). Intervention content (eg, types and frequencies of messages) is based on responses to these weekly assessments and participant phases. Our EndIT-Pilot results demonstrated that the app (Figure 2) worked very well, including being compatible with the 3 largest Cambodian cellular networks, properly delivering messages and weekly assessments, and reliably collecting and transferring data to our encrypted server [20].

**Figure 2 figure2:**
[figure not shown]
Insight app user interface example.

### Measures

#### Overview

CASI assessments occur in-clinic at baseline and at 3, 6, and 12 months. Participants also complete brief, weekly assessments via smartphone for the first 6 months of the study. Table 1 summarizes study measures at each assessment.

**Table 1 table1:** Study assessments.

Variable type and measure		Baseline	Weekly^a^	In-clinic follow-up (3, 6, and 12 months)
**Descriptors or potential moderators**				
	Demographics; health literacy [40]	✓		✓^b^
	Alcohol and drug use [41,42]	✓		✓
	CD4 lymphocyte count, viral load, tuberculosis coinfection, COVID-19–related variables, other health outcomes	✓		✓
	Dependence—Heaviness of smoking index [43]	✓		
	Self-report measures of antiretroviral therapy adherence [44]	✓		✓
**Adherence to treatment app**				
	Duration of phone on or off; numbers of messages or images or videos delivered, opened, and marked as viewed; numbers of weekly assessments opened and completed; data syncing frequencies	✓^c^	✓^c^	✓^c^
**Phase-based model mechanisms**				
	Wisconsin Smoking Withdrawal Scale (WSWS-2) [45]	✓^a^		✓^b^
	Reasons for quitting (intrinsic and extrinsic) [46]	✓		✓
	Contemplation Ladder [47,48]	✓	✓	✓
	Kessler Psychological Distress Scale (K6) [49]	✓	✓^b^	✓
	Positive and negative affect schedule (I-PANAS-SF) [50]	✓	✓^b^	✓
	Multidimensional Scale of Perceived Social Support [51]	✓		✓
	Self-Efficacy (related to smoking cessation) [52]	✓	✓^b^	✓
**Economic evaluation**				
	Five-level EQ-5D (EQ-5D-5L; for quality-adjusted life years calculations) [53]	✓		✓
**Primary outcome**				
	Smoking status (includes nicotine replacement therapy adherence, number of quit attempts, days smoking or abstinent, and other products) [54]	✓	✓^b^	✓
	Expired carbon monoxide [54]	✓		✓

^a^Delivered via smartphone app*.*

^b^Brief versions of the scales.

^c^Documented by digital date or time stamps in the smartphone app’s activity log.

#### In-Clinic Assessments at Baseline, 3-, 6-, and 12-Month Follow-Ups

Three forms of data are collected at these time points: CASI, expired carbon monoxide (CO) assessed with a CO monitor (CoVita Breath CO) to verify smoking status biochemically, and medical record data. The CASI assessment is administered at baseline (requires approximately 40 minutes to complete) and at each in-clinic follow-up visit (requires approximately 20 minutes to complete). Medical records are used to collect participants’ clinical information (with participants’ consent), including most recent CD4 counts, viral loads, medication, tuberculosis diagnosis or treatment, and other HIV-related or health conditions. Currently, ART patients at the selected clinics have CD4 lymphocyte count and viral load tests every 3-6 months. However, if participants’ medical records do not contain their CD4 lymphocyte count and viral load test results collected within the last 90 days, participants will be asked to provide a blood sample for these tests, following the current testing protocols at the ART clinics. At the final 12-month follow-up, we also will ask AM participants open-ended questions regarding usability, factors or features that helped them quit, barriers to cessation and how to overcome these barriers, and areas for improvement to the AM treatment program. Participants are compensated US $15 (~60,000 Cambodian riels) for each in-clinic visit.

#### Brief Weekly Smartphone Assessments

Participants are asked to complete brief weekly assessments via smartphones for 6 months, delivered by the Insight app (University of Oklahoma). Participants in AM receive 4-8 questions as described in the Automated Messaging section. Although completion of these brief treatment-driving assessments could be conceptualized as part of the AM treatment, we will attempt to balance the effects of these weekly contacts between the treatment groups. Therefore, participants in SC are also asked to complete a brief 4-item weekly assessment via the app. However, questions for SC participants are about diet. Participants’ responses are encrypted and stored on smartphones and synced to our secure server whenever a connection is active. Thus, our team has near real-time access to responses and we are able to track adherence carefully.

#### Primary Outcome

The primary outcome is smoking status 12 months post enrollment. Abstinence is defined as biochemically confirmed self-reported 7-day point prevalence abstinence with expired CO <6 ppm [54]. Secondary outcomes include 3- and 6-month biochemically confirmed abstinence. We will consider several other common outcomes, such as self-reported abstinence, length of abstinence, and number of quit attempts.

### Data Analysis Plan

#### Aim 1: Conduct an RCT to Evaluate the Efficacy of AM for Cambodian People With HIV Who Smoke

##### H1: At the 12-Month Follow-Up, Smoking Abstinence Will Be Higher in the AM (vs SC) Group

The primary outcome is biochemically verified 7-day point prevalence abstinence at the 12-month follow-up. The primary abstinence analysis will be intention-to-treat, with patients who do not complete the follow-up assessments considered to be smokers; however, we will explore other approaches for dealing with missing data (see Missing Data and Dropouts below).

To estimate the effect of AM on abstinence rates while accounting for the potential clustering of participants recruited from multiple clinic sites, we will use generalized linear mixed models (GLMM) analyses in which intervention groups (AM vs SC) will be estimated as a fixed effect, while the clinic will be modeled as a random effect nested within the treatment condition. Specifically, log binomial mixed models will be used to estimate the relative risk of quitting in the AM (vs SC) group. Although groups should be similar in baseline characteristics due to randomization, we will explore models that control for any demographic or clinical variables that differ between groups at baseline. We will also use GLMM to examine changes in abstinence rates over time while accounting for relevant baseline covariates. Similar GLMM or methodology, as appropriate for each outcome variable, will be used to examine other smoking-related variables, such as continuous abstinence, prolonged abstinence, and quit attempts. Statistical analyses will be performed using SAS (version 9.4; SAS Institute, Inc).

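### The primary model nests clinic within treatment although participants are randomised individually; if abstinence differs between clinics, this overstates the standard error of the AM effect and can cost power

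*Protocol article*

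**What the plan says.** The H1 section of the Protocol article's Data Analysis Plan gives treatment as a fixed effect and then says that "the clinic will be modeled as a random effect nested within the treatment condition". The stated purpose is "accounting for the potential clustering of participants recruited from multiple clinic sites". The scale is also fixed: "log binomial mixed models will be used to estimate the relative risk of quitting in the AM (vs SC) group".

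The design sections describe a different structure. Under Study Design, "Participants are people with HIV recruited through ART clinics in Phnom Penh", and participants are assigned at random after consent, 400 to each group. Under Baseline Assessment and Randomization, "Enrollees will be randomized to SC or AM via stratified randomization, with sex assigned at birth serving as the stratification variable". No sentence allocates clinics to arms.

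On the number of clinics, Participants and Eligibility says "There are currently 12 ART clinics or hospitals in Phnom Penh". Recruitment starts at the larger sites, and the team "may add additional clinic sites as needed to reach our accrual goals". The number finally used is therefore open.

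**The concern.** A clinic effect nested within treatment belongs to a trial in which whole clinics are allocated to arms, so that each clinic appears under one treatment only. Here individuals are randomised and each clinic should appear under both. The nested term then gives one clinic two independent effects, one for its AM patients and one for its SC patients.

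The clinic's general abstinence level is shared by its two groups of patients and largely drops out of AM minus SC. The nested model does not use this. It adds the between-clinic variance to the error of the treatment effect. At stake are the width of the primary confidence interval for the relative risk and the chance of detecting a real AM effect. The plan also carries similar models over to other smoking outcomes, so the clause may affect more than H1.

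**Working it through.** **What the article's own figures allow.** The pilot interval in the Introduction reproduces if 25 per arm is assumed (10/25 vs 2/25): relative risk 5.0, SE of log RR = sqrt(1/10 - 1/25 + 1/2 - 1/25) = 0.721, interval 5.0 x exp(±1.96 x 0.721) = 1.22 to 20.55. The target of 800 cannot be reproduced, because no 12-month rates, power, ICC or final number of clinics accompany it. The pilot rates would need only 27 per arm for 80% power. The inputs below are therefore assumptions.

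**Assumptions.** 400 per arm; 12-month abstinence 10% on SC and 16.7% on AM, which gives 80% power in a two-sided 5% comparison without clustering; 4 or 12 clinics of equal expected size; ICC 0 to 0.05; the same relative AM effect in every clinic; individual 1:1 allocation within clinics, not forced to balance. The ICC is turned into a between-clinic variance on the log scale by s² = ln(1 + ICC x 0.90/0.10). ICC 0.01, 0.02 and 0.05 give s = 0.29, 0.41 and 0.61. A clinic one SD above the centre then has exp(s) = 1.34, 1.50 or 1.84 times the central rate.

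**Mechanism.** With K clinics, the nested model adds about 2s²/K to the variance of log RR. For K = 12 and ICC 0.02, s² = 0.1655. The crossed SE is 0.188, so the nested SE should be about sqrt(0.188² + 2 x 0.1655/12) = 0.251. Simulation gives 0.241. The actual SD of the crossed estimates is 0.181, so the crossed SE is about right and the nested one is too large.

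With few clinics the formula is a poor guide. For K = 4 and ICC 0.02 it gives sqrt(0.189² + 2 x 0.1655/4) = 0.344, against 0.276 simulated. The power figures for the assumed rates are therefore taken from simulation.

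**Simulation.** Log-binomial random-intercept models fitted by maximum likelihood, Wald z test, 400 trials per row, both models fitted to the same data.

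| Clinics | ICC | SE nested | SE crossed | Power nested | Power crossed | Loss (points) |
|---|---|---|---|---|---|---|
| 12 | 0 | 0.194 | 0.189 | 80.0% | 81.2% | 1.2 |
| 12 | 0.01 | 0.219 | 0.189 | 67.0% | 78.2% | 11.2 |
| 12 | 0.02 | 0.241 | 0.188 | 60.8% | 83.0% | 22.2 |
| 12 | 0.05 | 0.278 | 0.187 | 45.3% | 79.0% | 33.7 |
| 4 | 0 | 0.196 | 0.189 | 75.2% | 78.2% | 3.0 |
| 4 | 0.01 | 0.247 | 0.190 | 59.3% | 79.7% | 20.4 |
| 4 | 0.02 | 0.276 | 0.189 | 43.8% | 78.0% | 34.2 |
| 4 | 0.05 | 0.290 | 0.196 | 42.1% | 76.9% | 34.8 |

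Monte Carlo error of a power near 60% is sqrt(0.6 x 0.4/400), or about 2.4 points.

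**Null case.** With no AM effect and ICC above 0, the nested test rejects in 1.8-3.5% of trials. The mean over the six settings is (2.2 + 2.5 + 3.5 + 2.8 + 1.8 + 2.0)/6 = 2.5%, with Monte Carlo error sqrt(0.025 x 0.975/2400) = 0.3 points. The crossed test averages (4.3 + 4.0 + 4.8 + 4.3 + 4.0 + 5.0)/6 = 4.4%. At ICC 0 the two models behave alike (6.8% vs 7.0% with 4 clinics, 3.5% vs 4.0% with 12).

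**Other assumed rates.** Simulations at 15% vs 23% (about 81% power without clustering, between-clinic SD 0.2-0.4, 150 to 300 trials per setting, error about 3-4 points) point the same way: 45-70% nested against 78-83% crossed with 4 or 6 clinics, and 63-77% against 80-84% with 12 clinics (SD 0.2-0.3).

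**If the pilot effect held.** At 8% vs 40%, even the harshest setting (4 clinics, ICC 0.05) leaves an effective 400/(1 + 99 x 0.05) = 67 per arm, and power is still above 99%.

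**The case against.** The strongest case on the other side has four parts.

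*The loss may be small.* The article speaks only of potential clustering. If clinics hardly differ, or the effect is as large as in the pilot, little is lost. This stands, and it limits the claim. The pilot rates do not settle the matter, since they are 2-month rates from 50 people. The clause also does its harm exactly where the clustering it was meant to handle exists.

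*A conservative test is safe.* False positives are indeed not inflated. But the interval is wider than the design warrants, and a real effect can be missed.

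*The AM effect may vary by clinic, and that variance belongs in the error.* True, but the form for this is a shared clinic intercept plus a clinic-by-treatment term. Nesting still treats the two arms of one clinic as independent.

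*It may be loose wording, and the analysis plan may be right.* Possibly. The article nevertheless states the structure, and read literally it specifies the wrong model. This is not a detail left for later.

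A reader might also add a loss from a t reference. With 2(K - 1) degrees of freedom and 4 clinics, a nominal 80% falls to about 64% even at ICC 0. That rests on an assumed degrees-of-freedom method. The article names the software but no such method, so this is not part of the conclusion.

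**Conclusion.** The primary model as written contradicts the randomisation: clinic is crossed with treatment, not nested in it. If abstinence differs between clinics, the nested model overstates the standard error of the AM effect and makes the primary test conservative. Under the assumptions shown, the power loss is about 11-20 points at ICC 0.01, 22-34 at 0.02 and about 34-35 at 0.05. It is about 1-3 points at ICC 0.

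A reader might infer that the clause will cost the trial much of its power. The documents do not support that unconditional reading, because they give no ICC, final number of clinics or 12-month rates. Nor does anything suggest that clinics were in fact allocated to arms, or that the false-positive rate is raised. The clause should be fixed, as a correctable misstatement of the primary model whose cost is possibly large but unknown.

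**What to change.** Replace the nesting clause in the H1 analysis with: *clinic will be included as a random intercept shared by both arms (crossed with treatment)*. Commit to this one form for the primary analysis, so that no choice between fixed and random clinic effects is left open. Examine variation of the AM effect between clinics in a sensitivity analysis that adds a clinic-by-treatment random term. Make the same substitution where the model is reused for other smoking outcomes.

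The cost is one sentence in the plan and one line of model code, with no new data. It should be done before outcomes are compared by arm, because a later change would look driven by the results.

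### The 12-month model leaves out sex, the stratification factor, and every prognostic covariate, and the exploratory adjusted models choose covariates by chance imbalance; the cost is modest and the cure nearly free

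*Protocol article*

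**What the plan says.** All references are to the Protocol article.

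- **Randomisation.** Under Baseline Assessment and Randomization, allocation is stratified, "with sex assigned at birth serving as the stratification variable". No other stratifier is named. Study Design plans 400 participants per arm.
- **Primary model.** Under Data Analysis Plan, Aim 1, H1, "intervention groups (AM vs SC) will be estimated as a fixed effect", and "the clinic will be modeled as a random effect nested within the treatment condition". The effect measure is a relative risk: "log binomial mixed models will be used to estimate the relative risk of quitting". Neither sex nor any baseline covariate is named for this comparison.
- **Adjusted models.** The same paragraph first notes that randomisation should make the groups alike, and then adds: "we will explore models that control for any demographic or clinical variables that differ between groups at baseline". It gives no threshold, candidate list or prognostic reason.
- **Change over time.** For a different analysis the paragraph uses a different principle: "We will also use GLMM to examine changes in abstinence rates over time while accounting for relevant baseline covariates".
- **Available predictor.** Table 1 shows the "Heaviness of smoking index" collected at baseline as the measure of dependence. Aim 3 lists biological sex and nicotine dependence level among the possible moderators.

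**The concern.** Two features pull against good practice.

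First, sex was important enough to constrain the allocation but does not appear in the model as described. Analysing as randomised normally means carrying the stratifier into the model.

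Second, the rule for choosing adjustment variables looks at the wrong property. In a properly randomised trial every observed baseline difference is chance. Its size says nothing about whether the variable predicts quitting. The rule can bring in irrelevant variables that happen to differ and leave out strong predictors that happen to look balanced. It will also rarely pick sex if the stratified allocation works as intended, because stratification is there to keep sex balanced. With no threshold or list, the word differ is left to the analyst.

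At stake are some precision in the primary comparison and the reproducibility of the adjusted results.

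**Working it through.** **No plan figure to reproduce.** The article gives no alpha, power, 12-month rates or dropout behind N=800. Effect sizes and thresholds below are assumptions, and ranges are shown.

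**1. How often chance picks a covariate.** Assume that a difference means p<0.05 and that the k candidates are independent. Then P(at least one picked) = 1 - 0.95^k.

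| k | 5 | 10 | 12 | 20 |
|---|---|---|---|---|
| P | 23% | 40% | 46% | 64% |

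If 3 of the 12 are truly prognostic, the chance of picking any of those three is 1 - 0.95^3 = 14%.

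**2. What sex alone is worth.** The article gives 49% men among ART patients, and smoking prevalence of 43%-65% in men and 3%-5% in women. The expected share of women among smokers is w = 0.51f / (0.51f + 0.49m).

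- Lowest (f=0.03, m=0.65): 0.0153/0.3338 = 4.6%, or 37 of 800.
- Highest (f=0.05, m=0.43): 0.0255/0.2362 = 10.8%, or 86 of 800.

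For a sex difference d in abstinence and overall abstinence p (both assumed), R² = w(1-w)d² / [p(1-p)]. The relative SE without the covariate is 1/sqrt(1-R²), and the sample-size equivalent is 800 × R².

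- w=0.046, d=0.05, p=0.25: R² = 0.0006, SE 0.03% larger, worth 0.5 participants.
- w=0.108, d=0.10, p=0.10: R² = 0.0107, SE 0.5% larger, worth 8.6 participants.
- Even at d=0.20, over p from 0.10 to 0.25, the gain is worth about 8 to 34 participants.

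**3. What prognostic covariates are worth.** With the same formulas, and starting from 80% power at two-sided 0.05:

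| R² | Participants (800 × R²) | Power |
|---|---|---|
| 0.02 | 16 | 80.8% |
| 0.05 | 40 | 82.0% |
| 0.10 | 80 | 84.0% |

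**4. Simulation of the three strategies.** N=800, 12 independent covariates of which 3 are prognostic, treatment log-odds 0.62, 4,000 trials per setting, linear-probability ANCOVA with robust SE and no clinic effect. The null spread of the estimate with weak predictors, 0.0219 = sqrt[4p(1-p)/800], implies p of about 11%.

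| Predictors (log-odds per SD) | Unadjusted | Picked by imbalance | Prespecified |
|---|---|---|---|
| weak (0.2, 0.2, 0.2) | 84.4% | 84.2% | 84.3% |
| moderate (0.4, 0.4, 0.4) | 84.1% | 84.3% | 85.9% |
| strong (0.6, 0.5, 0.4) | 81.9% | 82.4% | 85.0% |

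Entries are power. Prespecification gains about 0, 1.8 and 3.1 points. With moderate and strong predictors, imbalance picking recovers 0.2 and 0.5 points. Some covariate was picked in 44-47% of trials and a prognostic one in about 14%, in line with step 1.

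A second simulation (modified Poisson, two predictors, 7% women, 1,000 trials per setting) compared the mean SE of the log relative risk:

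- Log-odds 0.5 per SD: 0.1401 unadjusted, 0.1350 prespecified (3.6% lower), 0.1401 picked by imbalance.
- Log-odds 0.3 per SD: 0.1467, 0.1446 (1.4% lower), 0.1468.

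**5. Type I error.** In the first simulation each single analysis rejected in 4.6-5.6% of null trials. Taking the better of the unadjusted and imbalance-picked p-values gave 5.2-5.8%. The Monte Carlo SE is about 0.35 points.

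**The case against.** The strongest reply is that the primary analysis is fully fixed (treatment, clinic, log-binomial, intention-to-treat, missing counted as smoking) and that the criticised sentence only promises to explore further models. That stands. A reader might infer that chance defines the trial's main model, or that the primary result is biased or its error rate inflated. The documents do not support this: nothing lets an adjusted model replace the primary one, an unadjusted comparison of randomised arms is valid, and omitting a stratifier tends if anything to make the SE slightly conservative. The 46% describes how often an exploratory check acquires a covariate, not how often the trial's answer changes.

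It also stands that sex alone is numerically negligible here, that the gain with weak predictors is nil, and that neither simulation fits the planned log-binomial mixed model. The number of candidates and the 5% threshold are not in the article. Adding covariates to a log-binomial model also raises the risk of non-convergence, so the change is not free unless a fallback is named.

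The argument that this belongs to an unseen SAP carries only part of the way. A missing covariate list could be left there. But the article does not merely stay silent: it states a selection rule, and that rule is unsound even for a supporting analysis.

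**Conclusion.** The point holds as a modest improvement in design and wording, not as a threat to validity. As described, the 12-month model does not carry the stratification factor and uses no prognostic covariate, and the rule for the adjusted models selects on chance. There is no material type I error inflation. The loss is about 0.03-0.5% of the SE for sex alone (assuming 5-10 point sex differences and 10-25% overall abstinence) and roughly 0 to 3 power points for prognostic covariates, depending on how strongly they predict quitting. That the Heaviness of Smoking Index is such a predictor is an assumption; the article supports it only in so far as it names dependence as a possible moderator. The case for including sex is to match the analysis to the design; most of any precision gain would have to come from dependence. Whether clinic should be nested within treatment is a separate question and plays no part here.

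**What to change.** 1. Prespecify sex and baseline Heaviness of Smoking Index as fixed covariates in the 12-month abstinence model, to be included whatever the observed imbalance, and settle this before data lock.
2. Replace the rule based on variables that differ at baseline with this list.
3. Name a fallback estimator for non-convergence of the log-binomial mixed model, such as modified Poisson with robust SE or a standardised relative risk.
4. Keep the model without covariates as a sensitivity analysis.

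The cost is a change of wording in the plan. Both variables are already collected at baseline, so there is no added burden on participants and no change to sample size. The one real downside is the convergence risk, which the named fallback handles.
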